**Fig. 1 Fig1:**
[figure not shown]
Timeline of the robot-assisted stereotactic lesioning in the treatment of focal drug-resistant epilepsy study protocol

### Participant selection

The study is expected to enroll 240 participants. All participants will be recruited from the outpatient clinics of three centers and will be fully explained at the time of recruitment and will sign a written informed consent form. Minor participants and their legal guardians will also be fully explained about the study, and the written informed consent will be signed by their legal guardians.

Patients will be eligible for inclusion in the study only if all of the following criteria are applied:Age ≥ 3 years at enrollmentMeets the ILAE guidelines for the diagnosis of drug-resistant epilepsy with persistent disabling seizures (at least 1 or more per month); seizures persist after 2 years of standardized treatment with at least one or more first-line antiepileptic drugsWith a definite epileptogenic zone by preoperative comprehensive evaluation, which belonged to focal epilepsy, and are suitable for stereotactic RF-TC, stereotactic LITT, or resective surgeryAbility to understand and speak Mandarin Chinese

Patients with the following conditions will be excluded:

Epileptogenic foci cannot be accurately located or multiple epileptogenic foci are suspected after a comprehensive evaluation, which are not suitable for the operation included in this study.Pregnant or breastfeedingContraindications to surgeryHistory of previous operation for the purpose of treating epilepsyInclusion in any other clinical trialOther conditions that the researcher thinks he/she is not suitable to participate in the study

### Procedures for withdrawal or discontinuation

Participants can withdraw at any time. Eligible participants will receive three follow-up visits at 3, 6, and 12 months after surgery or until any of the following events occur.DeathEnd of the study periodLoss to follow-up: defined as referral to an epilepsy center that is not included in the study, or refusal to continue follow-up, or cannot be contacted by phone calls or WeChat for at least three times.Other epilepsy surgical treatment is required due to the conditionInvestigator considers it necessary for the participant to terminate the study

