**Methods:**

This is a multicenter, three-arm, randomized controlled clinical trial. The study will include patients older than 3 years of age with epilepsy who have had medically refractory seizures for at least 2 years and are eligible for surgical treatment with an epileptogenic focus as determined by multidisciplinary evaluation prior to randomization. The primary outcome measure is seizure outcome (quantified by seizure remission rate) at 3-month, 6-month, and 1-year follow-up after treatment. Postoperative neurologic impairment, spectrum distribution change of video electroencephalogram, quality of life, and medical costs will also be assessed as secondary outcomes.

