## Methods/design

### General study design

A multicenter, randomized controlled, parallel-group clinical trial will be conducted at Sanbo Brain Hospital, Beijing Tiantan Hospital, and Xuanwu Hospital. This study has been registered in the Chinese Clinical Trial Registry before the enrollment of participants (http://www.chictr.org.cn, registration number: ChiCTR2200060974).

Participant baseline information will be collected approximately 10 days before surgery, including participant demographics, seizure status, use of ASMs, neurological status, electroencephalogram (EEG), and magnetic resonance imaging (MRI) findings. The perioperative information of the participants will be recorded based on the surgical records and anesthesia records, including length of operation, amount of bleeding, complications, and cost of operation. The participants will be followed up for three times at 3, 6, and 12 months after the operation. The timeline of this study is shown in Fig. 1. The baseline information mainly includes the following:Seizure condition: seizure frequency (time/month), seizure duration, severity, etc.Neurological impairment: neurological function physical examination and National Institutes of Health Stroke Scale (NIHSS) score.Use of anti-seizure medications: type and dosage of drugs.Preoperative EEG examination: scalp EEG spectrum distribution, EEG Epileptogenic Index, etc.Preoperative MRI.Quality of life: using the Quality of Life in Epilepsy-89 scale for adults (ages 17–60) and the Quality of Life in Epilepsy-48 scale for children (ages 14–16). Patients not in the above age range will not be assessed for quality of life.Cognitive function: using the Chinese version of the Wechsler Intelligence Scale-IV and the Chinese version of the Wechsler Development Scale-IV.

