### Randomization and blinding

Randomization will be performed by independent investigators with the SAS (9.3, SAS Institute Inc., Cary, NC, USA) software. The resulting list of random numbers has been placed into sequentially numbered, sealed, opaque envelopes. Based on the information obtained from the envelopes, consecutively enrolled participants will be randomly assigned, in a 1:1 ratio, to stereotactic lesioning or classical epileptogenic zone resective surgery. Patients who are assigned to stereotactic lesioning surgery will be also assigned in a 4:1 ratio to a subgroup of RF-TC and a subgroup of LITT. The same group of neurosurgeons at different centers (three groups in total) will be responsible for different procedures for each participant.

Researchers and clinical research coordinators participate in the grouping process. Clinical research coordinators are responsible for informing patients, but they are not involved in the patient assessment and treatment process. All subjects and clinicians will be aware of the trial group assignments before surgical treatment, outcome assessors. However, outcome assessors and statisticians will not be aware of the subgroups of subjects

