#### Arm 2: Stereotactic EEG-guided RF-TC group

Patients enrolled in the stereotactic EEG-guided RF-TC group will undergo multicontact electrodes (RSDE-16/RSDE-12, Sinovation, China) implantation. After the intracranial electrodes are implanted, additional CT scans will be obtained to confirm their locations. Intracranial EEG recordings will be monitored to locate the epileptogenic zone. RF-TC will be performed on the contacts of the epileptogenic zone using a radiofrequency lesion generator (model R-2000B M1, BNS, China). A test heating will be performed first, and the patient will be monitored by EEG for 1 day. If the patient does not experience any unacceptable complications, RF-TC will be proceeded (3 W, 120 s). After RF-TC, the patient will be monitored by EEG for at least 1 night. The electrodes will then be removed, and the skin will be closed.

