### Outcomes

#### Primary outcome

The primary outcome is the participant’s seizure remission rate, which was defined by the following formula:$$\mathrm{Seizure\,remission\,rate}=\frac{\mathrm{Baseline\,seizure\,frequency}(\mathrm{per\,month}) -\mathrm{ Post}-\mathrm{op\,seizure\,frequency }(\mathrm{per\,month})}{\mathrm{Baseline\,seizure\,frequency}(\mathrm{per\,month})}\times 100\%$$

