### Statistical analysis

Statistical analysis will be mainly performed by researchers from Sanbo Brain Hospital, Capital Medical University, using the SAS 9.3 (SAS Institute Inc., Cary, NC, USA) software. Take the test level *α* = 0.05. The Kolmogorov-Smirnov test will be used to test whether the variables will be normally distributed. Measurement data conforming to normal distribution will express as mean ± standard deviation (‾X ± s), and measurement data not conforming to normal distribution will be expressed as interquartile range *M* (Q25, Q75). The *t*-test will be used to compare the normal distribution of continuous variables. The rank sum test will be used to compare the continuous variables that do not conform to the normal distribution. The chi-square test will be used to compare the categorical data. Univariate and multivariate methods will be used to analyze the preoperative and operative factors associated with seizure-free. Analysis of the primary outcome will be by intention-to-treat.

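### Intention-to-treat is stated for the primary outcome, but as written a randomised patient who has no operation has no scheduled visit and no outcome value

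*Protocol article*

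**What the plan says.** On the analysis population, the Statistical analysis section states: "Analysis of the primary outcome will be by intention-to-treat".

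On the outcome, the Primary outcome section gives the "seizure remission rate, which was defined by the following formula": baseline monthly frequency minus post-operative monthly frequency, divided by baseline.

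On timing, four places use the operation or treatment as the starting point:
- General study design: "The participants will be followed up for three times at 3, 6, and 12 months after the operation".
- Procedures for withdrawal or discontinuation: "Eligible participants will receive three follow-up visits at 3, 6, and 12 months after surgery".
- Abstract, Methods: the outcome is measured "at 3-month, 6-month, and 1-year follow-up after treatment".
- Table 1: the operation is time 0, and the main visits fall at 90 ± 7, 180 ± 14 and 365 ± 14 days.

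On what happens before the operation, Table 1 marks randomisation in the enrolment column (day −10) and has a separate allocation column at day −7. Randomization and blinding adds: "All subjects and clinicians will be aware of the trial group assignments before surgical treatment". The withdrawal section lets participants leave at any time.

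**The concern.** Intention-to-treat needs an outcome for everyone randomised. Here the outcome and the visits that measure it start only with an event that follows randomisation, and the patient already knows the arm by then. A patient who declines the operation or becomes unfit for it in that interval has a baseline frequency but no post-operative one, and no date from which to count 3, 6 or 12 months.

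An analysis of operated patients only is no longer a comparison of the groups as randomised. Open resection and minimally invasive lesioning are different prospects for a patient, so declining after disclosure need not be balanced. The article gives no data on this either way. What makes the point worth raising now is that it concerns data collection. An analysis plan can assign a value to a missing outcome, but it cannot recover an assessment that was never scheduled.

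**Working it through.** **Step 1. Follow one patient through the text.** The patient is randomised at about day −10, is told the arm, and declines the operation while agreeing to stay in the trial.

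- Baseline: "Participant baseline information will be collected approximately 10 days before surgery". This precedes the operation, so the first term of the formula would normally be available.
- Follow-up: no section gives a visit date that does not start from surgery, so nothing is scheduled.
- Outcome: the second term is a post-operative frequency, so the formula cannot be completed.
- Exit: the list of events that end follow-up does not include an operation not performed. The patient is not formally removed; there is simply no rule for follow-up.

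**Step 2. Inputs for scale.** From the article: 240 patients randomised 1:1 gives 120 lesioning and 120 resection. Expected withdrawal is 20%, so 0.20 × 240 = 48 patients, or 0.20 × 120 = 24 per arm. The article does not split this into losses before and after surgery, so the number never operated is unknown.

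Assumed, because the article gives no figure: operated patients in both arms have the same mean reduction m of 50%, 70% or 90%; unoperated patients stay at baseline (0% reduction); fractions f_L (lesioning) and f_R (resection) are not operated.

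**Step 3. Formula.**
- Operated-only difference, lesioning minus resection: m − m = 0.
- All-randomised difference: m(1 − f_L) − m(1 − f_R) = m(f_R − f_L).

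| f_L | f_R | m = 50 | m = 70 | m = 90 |
|---|---|---|---|---|
| 5% | 5% | 0 | 0 | 0 |
| 5% | 0% | −2.5 | −3.5 | −4.5 |
| 10% | 5% | −2.5 | −3.5 | −4.5 |
| 10% | 0% | −5 | −7 | −9 |
| 20% | 0% | −10 | −14 | −18 |
| 0% | 10% | +5 | +7 | +9 |

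Entries are percentage points of mean seizure reduction. The 20% row is an extreme: the whole expected loss of one arm (24 patients) would have to fall before surgery, with none in the other.

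**Step 4. Reading.** With equal fractions and equal effects the contrast does not move. It moves when non-operation is unequal, by m times the difference in fractions. It could also be biased with equal fractions if different kinds of patient drop out of each arm, which this simple model does not show.

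**The case against.** The strongest reply is that the article is silent on unoperated patients and does not exclude them. Rules for randomised but untreated patients often sit in an analysis plan or full protocol, and neither is shown. That is fair as far as scoring goes. It does not cover the visit schedule and the outcome definition, which the article does state, and always relative to the operation or treatment.

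A second reply is that the group may be small. Candidates must be suitable for the procedures, contraindications to surgery are excluded at entry, and the planned gap is only 7 to 10 days. This stands: nothing in the article shows that the number is large.

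Several stronger readings are tempting but not supported:
- A reader might infer that RF-TC patients stopped after the test heating are dropped, together with any harm they suffered. By then they have had electrodes implanted, which gives an operative date. No section removes them, and Table 1 schedules adverse events and neurological examination from day 7.
- A reader might infer that patients who receive another arm's operation also cannot be scored. They do have a post-operative frequency. The rule that a need for other epilepsy surgery ends follow-up leaves their handling unclear, but not impossible.
- A reader might object that neurological impairment has no stated analysis population. That is ordinary analysis-plan detail and no fault of the article.
- A reader might compare the shifts above with the 10% noninferiority limit. The Sample size section does not tie that limit to mean seizure reduction, so the comparison is not valid.

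**Conclusion.** The point holds for patients who have no operation at all. For them the stated intention-to-treat analysis has neither a scheduled assessment nor a defined outcome, and followed literally it would omit them. It is not established that the trial will be an operated-only comparison or that its result will be biased. Bias in the difference requires non-operation, or the kind of patient not operated, to differ between arms, and the article gives no figure for either. The 5 to 9 points at 10% non-operation in one arm only, and the zero shift at equal rates, are illustrations resting on an assumed mean of 50% to 90% and no change in unoperated patients. The text should be amended because the gap is clear and cheap to close, and data not collected during follow-up cannot be recovered later.

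**What to change.** 1. Keep surgery-dated visits for operated patients. In General study design, the withdrawal section and Table 1, add that a randomised patient who is not operated takes the planned surgery date, or a fixed number of days after randomisation, as day 0.
2. Collect seizure frequency from these patients at 3, 6 and 12 months, by visit or by phone, provided they still agree to be followed.
3. In the Primary outcome formula, replace the post-operative term with seizure frequency at the follow-up assessment.
4. In Statistical analysis, state that these patients are analysed in their allocated arm.
5. For RF-TC patients stopped after electrode implantation or test heating, state that the implantation date is day 0 and that they stay in the RF-TC arm. This concerns dating and analysis only, not whether treatment should proceed.

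Re-dating every visit from randomisation is a possible alternative but a worse trade. A shift of about 10 days fits the ±14-day windows but exceeds the ±7-day window at 3 months, and time since surgery would then vary with the waiting time.

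The cost is a wording amendment and a few extra contacts; the trial already uses phone contact for follow-up. The resulting estimate includes patients who did not have the assigned operation, so an operated-only analysis should be kept as supporting. Patients who withdraw from follow-up altogether remain missing under any schedule.

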### Sample size

According to earlier studies and the previous work of our research team, the effective rates of stereotactic EEG-guided RF-TC, MRI-guided stereotactic LITT, and resective surgery are similar, and the rates of postoperative neurological impairment are 2%, 2%, and 11%. We expect to use a one-sided 95% confidence interval, a noninferiority limit of 10%, and an expected withdrawal rate of 20%. Therefore, we expect to enroll a total of 240 patients in this study. Patients will be recruited from outpatient and MDT with strict inclusion criteria.

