### Data management

All baseline information and outcome-related data will be evaluated and collected by two experienced clinicians (one neurologist and one neurosurgeon). Detailed data collection and follow-up time are shown in Table 1. Each patient’s data will be completed into an electronic case report form (eCRF) by an independent clinical research coordinator. Participants will be given trial information to improve participation. In order to ensure the completion of the follow-up, we will contact participants by phone in advance.

**Table 1 Tab1:** Participant timeline

**Study period**	**Enrollment**	**Allocation**	**Operation**	**Follow-up**	**Follow-up**	**Follow-up**	**Follow-up**
**Time point**	− 10 days	− 7 days	0	7 ± 2 days	90 ± 7 days	180 ± 14 days	365 ± 14 days

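### Referral to a non-study epilepsy centre counts as loss to follow-up and ends later visits, so reachable patients who have not refused lose their remaining primary-outcome values by rule

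*Protocol article*

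**What the plan says.** The section on procedures for withdrawal or discontinuation sets the follow-up rule: "Eligible participants will receive three follow-up visits at 3, 6, and 12 months after surgery or until any of the following events occur". Loss to follow-up is one of the listed events. It has three alternative forms: referral outside the trial ("defined as referral to an epilepsy center that is not included in the study"), refusal to continue, or a participant who "cannot be contacted by phone calls or WeChat for at least three times". Any one of them is enough.

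The abstract says when the outcome is needed: "The primary outcome measure is seizure outcome (quantified by seizure remission rate) at 3-month, 6-month, and 1-year follow-up after treatment". Table 1 schedules the seizure remission rate at the same three visits. The primary outcome section defines that rate as the percentage reduction in monthly seizure frequency from baseline.

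The statistical analysis section states: "Analysis of the primary outcome will be by intention-to-treat". The only retention measure described under data management, apart from giving participants trial information, is this: "In order to ensure the completion of the follow-up, we will contact participants by phone in advance".

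**The concern.** Referral is a change in where a patient receives care. It does not show that the patient cannot be found or is unwilling to answer. The article nevertheless classes it as loss and stops the visits.

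The study treatment is a single operation, so ending follow-up afterwards withdraws no study treatment and only stops data. The data at stake are light, because the primary outcome needs only a monthly seizure count, and the trial already contacts patients by phone and WeChat.

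Two things are at stake. First, randomised patients drop out of the later primary analysis through a definition and not through any real obstacle, which conflicts with the aim of intention-to-treat. Second, the loss may not be random. Patients whose seizures continue are plausibly the ones sent elsewhere. The randomization and blinding section says that patients and clinicians know the assigned group, so referral could also differ by arm.

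**Working it through.** **1. Reading the clauses together.**
- Refusal is its own form of loss, so the referral clause cannot be meant for patients who refuse.
- Failed contact is its own form of loss, so the referral clause cannot be meant for patients who cannot be reached.
- What the referral clause adds is therefore the patient who was referred, has not refused and has not been found unreachable.
- No other section of the article provides for collecting the seizure count after a referral. The advance phone call in data management is aimed at completing scheduled visits, and those visits have ended for this patient.

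**2. Which primary values are lost.** Only visits after the event are lost:

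| Referral occurs | Values kept | Values lost |
|---|---|---|
| before the 3-month visit | none | 3, 6, 12 months |
| between 3 and 6 months | 3 months | 6, 12 months |
| between 6 and 12 months | 3, 6 months | 12 months |

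The 12-month value is lost in every case. The primary outcome section does not choose among the three time points, so each of them matters.

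**3. The planned allowance.** The sample size section expects 20% withdrawal from 240 patients: 0.20 × 240 = 48, leaving 192. The article does not say how much of the 48 is referral, so the share due to this clause cannot be calculated.

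**4. Illustration of direction only.** All inputs here are assumptions. Let both arms have a true mean remission of 70%. Let referred patients average 20%, and analyse only those still followed. With referral proportion r, the observed mean is (70 − 20r)/(1 − r).
- r = 5% (6 of 120): (70 − 1)/0.95 = 72.63
- r = 10% (12 of 120): (70 − 2)/0.90 = 75.56
- r = 15% (18 of 120): (70 − 3)/0.85 = 78.82
- r = 20% (24 of 120): (70 − 4)/0.80 = 82.50

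If one arm refers 5% and the other 10%, 15% or 20%, the spurious differences are 75.56 − 72.63 ≈ 2.9, 78.82 − 72.63 ≈ 6.2 and 82.50 − 72.63 ≈ 9.9 percentage points. If both arms refer the same proportion of equally poor responders, the difference is zero, although each arm's mean is overstated. The bias between arms in this example thus depends on unequal referral, for which the article gives no evidence either way.

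**The case against.** **The article is condensed.** Contact windows and tracing steps may be in the full protocol. This largely stands for the failed-contact clause. Three failed contacts is a usual kind of rule and describes someone who was not reached. Its weakness is only that the article states no window and no way back. It does not rescue the referral clause, which is a stated rule and not an omission.

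**Intention-to-treat may mean analysis by allocated arm, with missing data handled in an analysis plan not shown.** This is fair, and values recorded before the referral are kept. No analysis plan, however, can restore values that the protocol has stopped collecting.

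**Counts taken after referral may be contaminated.** The interventions section asks participants not to change the type or dose of medication, and another centre may change it. This stands as a cost. An intention-to-treat analysis accepts such changes, and recording them lets their effect be examined.

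**Stronger readings are not supported.**
- A reader might infer that the rule could bring a truly worse arm inside the 10-point limit. Assume true success of 60% v 75% and loss of 5% of successes. Losing 45% v 30% of failures then shrinks the observed difference from −15 to −8.1 points, and losing 50% v 20% shrinks it to −4.1. These cases need total losses of about 21% v 11% and 23% v 9% by arm, and they charge all loss to the definition. They also use a binary success rate, whereas the primary outcome is a percentage reduction. With 40% of failures lost in both arms, the difference is −12.2, still outside the limit. These figures are illustrations and not an estimate for this trial.
- A reader might also count the investigator's power to end participation as part of this fault. It is a separate listed event, outside the definition of loss, and nothing shows that it would be used on patients who could still give data.

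**Conclusion.** The point holds for the referral clause. As written, a randomised patient who is reachable and has not refused loses all primary-outcome values after the date of referral, always including the 12-month value. This rests on the wording alone and needs no assumption.

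That the loss is informative is plausible, because continuing seizures are a natural reason for referral and clinicians know the allocation. It is not demonstrated, and arm-dependent referral is a possibility only. The size of any bias or loss of precision cannot be derived without a referral rate.

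The failed-contact clause is a secondary matter of clarification. The protocol should be amended, since the correction is cheap and uncollected outcomes may not be recoverable later.

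**What to change.** In the section on withdrawal or discontinuation:

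1. Delete referral to a non-study centre from the definition of loss. Continue to collect the monthly seizure count at 3, 6 and 12 months by phone or WeChat unless the participant refuses.
2. Record the date of and reason for each referral, and any change of anti-seizure medication made elsewhere, and report them by arm.
3. Secondary: treat three failed contacts as one missed visit and try again at each later visit. Declare loss only when the 12-month window closes without contact.

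The cost is a short amendment with ethics review, and some extra calls. Some counts would be taken remotely and not at a clinic visit, and some would reflect treatment changed at another centre. The amendment should say that the primary analysis includes them. No study treatment or clinical rule changes.
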